9.3 Reporting and Registration of Adverse Events

- AEs will be recorded by clinicians in the research team at each contact point with a study participant and reported in the REDCap documentation system and a manual standardized AE log template and serious events will be reported to the relevant authorities.

Serious adverse events (SAEs) will be reported within 24 hours of the investigator becoming aware, in accordance with Article 41 of CTR 536/2014.

- Suspected Unexpected Serious Adverse Reactions (SUSARs) will be reported to all investigators and Läkemedelsverket (LVM).

- All AEs and SAEs will be collected from Dosing 1 until final follow-up at 12 months.

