4.3 Primary Endpoint

- **Safety:** Incidence of adverse events (AEs) and serious adverse events (SAEs) during the trial period.

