**Preparation Phase**

- Preparation Session 1 & Baseline Assessment (Week 0): Psychoeducation about psilocybin, breathing and relaxation techniques, rapport-building with therapists, and discussion of expectations and concerns.
  Includes full baseline assessments (list provided as attachment to protocol:
  - Expectation of Treatment Scale (ETS-BF)
  - Readiness and Motivation Questionnaire (RMQ)
  - General Change Mechanisms Questionnaire (GCMQ)
  - Patient Health Questionnaire (PHQ-9)
  - Generalized Anxiety Disorder scale (GAD-7)
  - Eating Disorder Examination Questionnaire (EDE-Q )
  - Columbia-Suicide Severity Rating Scale (C-SSRS)
  - Brief Psychiatric Rating Scale – Extended (BPRS+)
  - Satisfaction With Life Scale (SWLS)
  - Positive and Negative Affect Schedule (PANAS)
  - Harmony in Life Scale (HILS)
  - Ten Item Personality Inventory (TIPI)
  - Honesty-Humility Scale (HH)EGON
- Visual size estimation (EGON)

Vital signs, ECG, blood glucose, urine drug screening, pregnancy test, fMRI, BMI and blood sampling for BDNF and safety labs are also conducted.

Preparation Session 2 (Week 1): Conducted 7–10 days after Preparation 1, and 2–3 days before psilocybin dosing.

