**Primary Endpoint Week 9**

Includes full safety and outcome evaluations:
- fMRI

- blood sampling (including glucose, liver, kidney, glucose, BDNF)
- Vital signs, ECG, U-tox

- BMI
- AE/SAE monitoring
- Readiness and Motivation Questionnaire (RMQ)
- General Change Mechanisms Questionnaire (GCMQ)
- Patient Health Questionnaire (PHQ-9)
- Generalized Anxiety Disorder scale (GAD-7)
- Eating Disorder Examination Questionnaire (EDE-Q)
- Columbia-Suicide Severity Rating Scale (C-SSRS)
- Brief Psychiatric Rating Scale – Extended (BPRS+)
- Satisfaction With Life Scale (SWLS)
- Positive and Negative Affect Schedule (PANAS)
- Harmony in Life Scale (HILS)
- Ten Item Personality Inventory (TIPI)
- Honesty-Humility Scale (HH)

- Visual size estimation (EGON)

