**All concomitant medications will be carefully documented and considered in the interpretation of clinical outcomes.**

The following psychiatric medications are prohibited in participants receiving psilocybin due to known or potential pharmacodynamic interactions and risk of attenuated psychedelic effects or adverse reactions:

•Monoamine oxidase inhibitors (MAOIs)

•Tricyclic antidepressants (TCAs)

•Benzodiazepines ≤ 2 mg lorazepam equivalents per day (must not be taken within 12 hours prior to psilocybin administration)

•Antipsychotics

•Lithium

Participants will undergo a thorough medication review during screening to identify potential pharmacological interactions. Medications with prohibited serotonergic activity require washout periods of 2–4 weeks before psilocybin dosing according to clinical practise guidelines.

- Participants who cannot safely discontinue contraindicated medications will not be included in the study.

- The washout will primarily be monitored by phone and a medical doctor within the research team appointed by the principal investigator, with in-person visits if needed. Participants who exceed the 8-week limit without dosing will be re-evaluated for eligibility by the principal investigator. The time from screening to first dosing shall not exceed 8 weeks regardless of washout status.

- Psychotherapy and other non-pharmacological treatments will be allowed throughout the study period as TAU if not deemed an exclusion criterion. Temporary daycare after discharge will be considered part of TAU rather than non-pharmacological treatment.

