8.2 Methods for Measurement of Endpoints for Clinical Safety

Continuous clinical safety monitoring will be performed by licensed healthcare professionals at Lund University Hospital throughout the trial, from baseline to the final 12-month follow-up. The safety evaluations cover physical, biochemical, and psychological parameters relevant to psilocybin administration.

For a complete list and overview, please visit the Schedule of Assessments attached to the protocol.

- **Hepatic and renal function:** Blood samples will be collected to assess creatinine, albumin, PK-INR, ALAT, ASAT, GT, ALP, and bilirubin levels. These assessments will occur during screening, at baseline (Week 0), after each psilocybin dosing, at the primary endpoint, and at the 6-month follow-up (Week 24).
- **Glucose:**Measured at the same time points as above – during screening, baseline, after each dosing, at the primary endpoint, and the 6-month follow-up. Additionally, glucose levels will be assessed at 9- and 12-month follow-up visits.
- **Urine toxicology (U-tox):** Drug use screening will be performed at baseline, and again at 6-, 9-, and 12-month follow-ups.
- **Cardiovascular parameters (ECG, blood pressure, pulse):** These will be measured at screening, baseline, after each dosing session, during the first integration sessions (1 day post-dosing), and at all subsequent follow-ups.
- **Assessment of suicidality and psychiatric safety:** Suicidality will be assessed using the Columbia-Suicide Severity Rating Scale (C-SSRS) at baseline, after each psilocybin session, during integration, and at all follow-ups. Psychiatric symptoms will be monitored using the Brief Psychiatric Rating Scale – Extended (BPRS+).
- **Mental health symptoms:** Self-report instruments including the PHQ-9 (depression), GAD-7 (anxiety), and other measures will be completed at baseline, at each integration visit, at the primary endpoint, and at the 12-month follow-up.
- **Adverse Events (AE/SAE):** Spontaneously reported by participant patients or by clinician at all in-person visits from first dosing onwards, including all integration and follow-up assessments.

All data will be collected under Good Clinical Practice (GCP) conditions and entered the electronic case report form (eCRF) by trained personnel.

9. Handling of Adverse Events

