9.1 Definitions

- *Adverse Event (AE):* Any untoward medical occurrence in a subject to whom a medicinal product is administered and which does not necessarily have a causal relationship with this treatment.

*Adverse Reaction (AR):* In the pre-approval clinical experience with a new medicinal product or new use of a medicinal product, and particularly as the therapeutic dose(s) may not be established, all noxious and unintended reactions to the medicinal product related to any dose should be considered an adverse reaction (AR). The phrase “reaction” to a medicinal product means that the causal relationship between the medical product and an adverse event is at least a reasonable possibility, that is the relationship cannot be ruled out.

*Serious Adverse Event (SAE) Serious Adverse Event (SAE): Any untoward medical occurrence that at any dose requires inpatient hospitalization or prolongation of existing hospitalisation, results in persistent or significant disability or incapacity, results in a congenital anomaly or birth defect, is life-threatening, or results in death.*

*Medical and scientific assessment will be made to determine if an event is serious.*

*Suspected Unexpected Serious Adverse Reactions (SUSAR)*: An adverse reaction/event that is unexpected, serious, and suspected to be caused by the treatment, i.e. adverse reactions/events that are not included in the RSI section of the Investigator’s Brochure (IB) or SmPC.

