10.2 Statistical Analyses

This will be an open label, two-arm, active comparator (TAU; treatment as usual), , randomized controlled, between- and within-subjects, design in up to 40 completing patients meeting DSM-5 criteria for eating disorders. The patients will be randomly allocated to the psilocybin treatment-arm. The study analyses will enable comparison of efficacy between psilocybin-treatment and treatment as usual, as well as longitudinal within-patient efficacies.

- Primary Baseline Analyses:
  The primary analyses will involve descriptive statistics for demographic and baseline characteristics, ensuring comparability across groups, and control for follow-up measurements.
- Primary Endpoints analysis
- We will analyse differences in the number of participants and severity experiencing AE/SAE between the groups standardized forms for AE/SAE capturing: Event description, Start and end dates, Severity (e.g., mild, moderate, severe), Relatedness to intervention (assessed by safety review committee), Action taken.

The primary statistical methods will be:

- Descriptive Frequencies and Percentages.
- Comparing Proportions (Most Common for "Incidence") (Chi-squared test (or Fisher's Exact Test): Fisher's exact test is preferred for small cell counts (<5).
- Risk Ratio (RR) or Odds Ratio (OR) with Confidence Intervals: Report these measures of effect size to quantify the magnitude and precision of the difference between groups. An RR > 1 would indicate a higher risk in the intervention group.
- Comparing Severity and Relatedness is assessed with Mann-Whitney U test or Student t-test to compare severity distributions between groups.
- Secondary Endpoints:
  For secondary endpoints (e.g., changes in fMRI connectivity, BDNF, rating scales), group comparisons, including t-test, ANOVA, and Repeated Measures ANOVA will be utilized. When controlling for variables such as individual differences, ANCOVA or MANCOVA will be utilized. Principal component analysis (PCA) or independent component analysis (ICA) may be applied to identify patterns in fMRI data. Task-based fMRI data will be analysed using univariate models to investigate treatment effects in syndrome-related neural circuits (Celeghin et al., 2023; Bronleigh et al., 2022). Endpoints include longitudinal between- and within-person analyses.

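### Adverse events are collected from the first psilocybin dose, which gives the TAU arm no start date for the primary between-arm safety comparison

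*Protocol*

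**What the plan says.** The primary endpoint in section 4.3 is "Incidence of adverse events (AEs) and serious adverse events (SAEs) during the trial period". Section 5.2 defines each patient's trial duration as screening to week 52.

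The primary endpoint analysis in section 10.2 is comparative: "We will analyse differences in the number of participants and severity experiencing AE/SAE between the groups". It uses chi-squared or Fisher tests, risk or odds ratios with confidence intervals, and a comparison of severity distributions.

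Collection starts later than the trial period does. Section 9.3 states "All AEs and SAEs will be collected from Dosing 1 until final follow-up at 12 months", section 11.2 repeats that start, and section 8.2 has AEs reported "at all in-person visits from first dosing onwards, including all integration and follow-up assessments". The control arm in section 5.1 is TAU alone. Section 7.4 lets TAU participants move to psilocybin after the six-month follow-up if the safety committee is satisfied.

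On the period before dosing, section 7.3 says "Medications with prohibited serotonergic activity require washout periods of 2–4 weeks before psilocybin dosing", and sections 5.2 and 7.3 allow up to 8 weeks from screening to first dose. Section 10.1 directs the safety analyses primarily to participants who received at least one dose.

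**The concern.** A between-arm comparison of incidence needs the same clock and the same means of finding events in both arms. Here the clock starts at an event that only one arm has.

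- **No start for TAU.** No section gives the control arm a first day of AE collection, so site staff would have to choose one.
- **Pre-dosing events are lost.** Events during tapering or washout undertaken for the trial fall before Dosing 1. Section 5.1 itself names withdrawal symptoms and destabilisation as risks of stopping antidepressants.
- **No rule after a switch.** Collection runs to month 12, but TAU participants may receive psilocybin after month 6. Nothing says to which arm, or to which analysis, their later events belong.
- **Possibly unequal ascertainment.** Section 9.3 has AEs recorded at each contact. The contacts described before Week 9 are dosing and integration visits.

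An analysis plan can choose among recorded events, but it cannot recover events that the protocol never told sites to collect.

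**Working it through.** The protocol states no AE rate, effect size or power, so there is no figure of its own to reproduce. The check sets the sections side by side and then asks how large the ascertainment effect could be.

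**Start and end of the window**

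| Section | Start | End |
|---|---|---|
| 4.3 with 5.2 | screening | week 52 |
| 8.2, 9.3, 11.2 | first psilocybin dose | month 12 |
| TAU arm, any section | not stated | month 12, no rule at the switch |

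Section 5.2 also does not say at which visit randomisation takes place.

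**Effect of the start date alone.** Assume 1 AE per patient-year, followed to week 52, with P(any AE) = 1 − exp(−weeks/52).

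- From Dosing 1 (week 1): 1 − exp(−51/52) = 0.625.
- From week 0: 1 − exp(−52/52) = 0.632.
- From a screening visit 8 weeks before dosing (week −7): 1 − exp(−59/52) = 0.678.

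On this assumption of a constant rate the start date alone moves incidence little. It would matter more if events cluster in a taper, for which the protocol gives no rate.

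**Contacts to Week 9.** Section 5.2 lists 8 for the psilocybin arm: Dosing 1, Integration 1 to 3, Dosing 2, Integration 4 and 5, and Week 9. For TAU the body text offers only Week 9. After that, months 3, 4, 5, 6, 9 and 12 carry no arm restriction.

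Contacts are not weeks. Integration 1 and 4 fall on the day after dosing, and the week before Dosing 1 lies outside the window. If each contact surfaces only the preceding week, the psilocybin arm covers five distinct weeks (1–2, 2–3, 3–4, 4–5 and 8–9). TAU covers one (8–9).

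**Illustration with no true difference.** Assume 0.1 AE per week in both arms, so that P(any AE) = 1 − exp(−0.1 × weeks covered).

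| Recall at each visit | Weeks covered, psilocybin vs TAU | P(any AE) | Risk ratio |
|---|---|---|---|
| One week | 5 vs 1 | 0.393 vs 0.095 | 4.1 |
| Four weeks | 8 vs 4 | 0.551 vs 0.330 | 1.7 |
| Everything since the start | 8 vs 8 | 0.551 vs 0.551 | 1.0 |

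With one-week recall, 0.05 AE per week gives 0.221/0.049 = 4.5, and 0.2 per week gives 0.632/0.181 = 3.5. The treatment description in section 5.2 gives two integration visits per dose, not five in total. Dropping Integration 3 leaves four weeks against one, and 0.330/0.095 = 3.5 at 0.1 per week.

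The rates and recall periods are assumptions. The table shows that the result turns on recall, which the protocol does not specify.

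**The case against.** The strongest reply is that collection in TAU is plainly intended. AE/SAE monitoring is listed at Week 9 and at months 3, 4, 5, 6, 9 and 12 without restriction by arm, section 9.3 speaks of each contact with a study participant, and section 9.6 evaluates trends by treatment arm. This stands. A reader might infer that TAU would contribute no events at all, but the documents do not support that. What is missing is the date from which TAU events count.

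The contact imbalance is read from the body text only. Section 8.2 refers to an attached Schedule of Assessments, which may list TAU visits before Week 9. Section 10.2 records AE start and end dates, so a Week 9 visit can capture earlier events. Both points stand, and they are why no single risk ratio or p-value should be quoted. A reader might also multiply 8 contacts by one week each and obtain 0.551/0.095 = 5.8. That counts overlapping weeks twice, includes a week outside the window, and assumes a recall period found nowhere in the protocol.

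Two further readings go too far. The AE definition, "Any untoward medical occurrence in a subject to whom a medicinal product is administered", need not mean psilocybin and can cover medicines given under TAU. The label "Primary Endpoint Week 9" is a visit heading, which section 4.4 uses as a timepoint for secondary measures, so it is not a rival AE window.

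The washout group may be small. Section 7.3 does not prohibit SSRIs or SNRIs as such, calls TCA use rare, and expects users of antipsychotics or lithium generally not to qualify. That limits the number affected but does not bring their events into the endpoint.

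Finally, section 10.1 focuses safety on the dosed cohort, for which Dosing 1 is a coherent start. But that cohort contains no TAU participant in the randomised period, so it cannot supply the comparison in section 10.2. Section 15 ties reporting to the six-month follow-up without the switch, which suggests a natural cut-off. The AE sections do not use it.

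**Conclusion.** The point holds. Three sections start AE/SAE collection at the first psilocybin dose, while the primary analysis compares arms over a period that section 5.2 begins at screening. TAU has no stated start, pre-dosing washout events lie outside the endpoint, and events after a switch are unassigned. These three gaps follow from the text and need no assumption.

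Unequal ascertainment before Week 9 is possible but not established, because it depends on a schedule that is not shown. Assuming 0.1 AE per week, no true difference and the visits in the body text, the expected risk ratio to Week 9 ranges from 1.0 with full recall to about 4 with one-week recall. That range shows how sensitive the comparison is and does not forecast the result. It should be fixed before enrolment, because events in uncollected weeks cannot be reliably reconstructed later.

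**What to change.** 1. Amend sections 8.2, 9.3 and 11.2 so that AEs and SAEs are collected in every participant of both arms from one arm-neutral start: randomisation, or the start of trial-related tapering if that is earlier. State in section 5.2 where randomisation falls in the visit sequence.
2. State one window for the between-arm comparison, align section 4.3 with it, and end or censor it at the switch for TAU participants. Report events after a switch separately.
3. Base the between-arm test on SAEs and on AEs elicited with the same questions, covering the time since the last common visit, at visits common to both arms.
4. Keep the dosed cohort in section 10.1 as a single-arm descriptive safety summary from Dosing 1.

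The cost is a protocol amendment, which section 12.2 treats as substantial where safety procedures change, and an earlier AE start date in the eCRF. Short AE phone calls to the roughly 20 TAU participants in the dosing weeks would even out ascertainment further. They are optional if the test uses common visits.

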9.4 Follow-up of Adverse Events

Follow-up visits will be scheduled for all participants experiencing AEs to ensure resolution and ongoing safety.

- Participants with unresolved AEs at the end of the trial will be monitored until resolution or stabilization.
- For SAEs, additional follow-ups will be scheduled at least every two weeks until resolution. The frequency can be changed by the Safety Review Committee or Principal Investigator.

9.5 Safety Review Committee

A Safety Review Committee will oversee trial safety and make recommendations on trial continuation. The committee will receive notification on all SAEs and SUARs by the research team within 24 hours.

The committee will review safety data quarterly and after every interim analysis (after every 10 psilocybin dosing sessions). They may recommend protocol modifications, halting recruitment, or terminating the trial based on emerging risks.

The committee will include at least two clinical and senior psychiatrists, a clinical pharmacologist, and a statistician, not affiliated with the research team, but not from an independent organisation.

No formal Data Monitoring Committee will be used in this trial.

9.6 Annual Safety Report (ASR)

An annual safety report will be submitted to regulatory authorities by the study coordinator in collaboration with the principal investigator.

The report will include a summary of all AEs, SAEs, SUSARs, and risk-benefit analyses to date. Specific trends in adverse events by treatment arm will also be evaluated.

9.7 Procedures in Case of Emergencies and Overdose

- Emergency protocols are in place, including immediate medical care and monitoring.

- In case of an overdose, the participant will be transferred to an emergency facility. Emergency kits, including benzodiazepines for anxiety or seizures, will be available during all dosing sessions.

9.8 Pregnancy Management

Recommendations related to contraception and pregnancy testing in clinical trials based on version 1.2 available at https://www.hma.eu/about-hma/working-groups/clinical-trials-coordination-group.html.

Woman of childbearing potential (WOCBP) is defined as any biologically female person post-menarche until menopause, unless surgically sterilized.

9.8.1 Prevention of Pregnancy During the Study

- Participants of childbearing potential must agree to use a highly effective contraceptive method throughout their participation in the study and for at least two months following their final psilocybin administration session. Highly effective contraceptive methods: combined (estrogen and progestogen containing) contraception associated with inhibition of ovulation, oral intravaginal transdermal hormonal, progestogen-only hormonal contraception associated with inhibition of ovulation, oral injectable implantable, intrauterine device (IUD), intrauterine hormone-releasing system, bilateral tubal occlusion, vasectomised partner, sexual abstinence.

9.8.2 Pregnancy Testing

- All participants of childbearing potential will undergo a urine pregnancy test during screening.
- A urine pregnancy test will be conducted at baseline (prior to the first psilocybin administration) and before the second subsequent psilocybin dosing session.
- Additional pregnancy tests may be performed if clinically indicated during follow-up visits or as deemed necessary by the investigator.

9.8.3 Exclusion of Pregnant Participants

- Participants who are pregnant or nursing at screening or who plan to become pregnant during the study period will be excluded.
- Participants must confirm their commitment to avoiding pregnancy during the study as part of the informed consent process.

9.8.4 Immediate Action Upon Pregnancy Detection

- If a participant becomes pregnant during the study:
  - Psilocybin administration will be discontinued immediately.
  - Appropriate obstetric care referrals will be provided, and the participants will receive follow-up to ensure their well-being.

Rationale for Precautions

- Psilocybin’s impact on reproductive health and fetal development is unknown due to the lack of reproductive toxicology studies and therefore will be considered to belong to the risk category of “demonstrated/suspected teratogenicity”, in which the participants must use contraception considered to be highly effective as listed above. These measures aim to mitigate any potential risks and prioritize participant safety.

10. Statistics

